##### COVID19 risks mitigation

The COVID19 pandemic presents a very challenging time for community and local governments with various restrictions that may be posed by the Australian government.

Potential delays to site construction (e.g., due to shortage of staff, shipping delays) and/or data collection may occur. We will work closely with the partners to accommodate flexibility in our approach and the project’s timeline will be adjusted based on site upgrade completion. We also anticipate that usage and access to the parks may be impacted by lockdown periods, hence data collection periods (observation and intercept interviews) may need to be adjusted to avoid periods where access to outdoor equipment is prohibited.

Cleaning and hygiene practice—Hand sanitizers will also be available for both staff and participants to use at the beginning and completion of each exercise session, or during exercise sessions if required. The equipment will be regularly cleaned using detergent solution/disinfectant spray or wipes.

Outdoor training and physical distancing—Most training sessions will be provided outdoors which reduce the risk of transmission. Physical distancing will be maintained during data collection where possible (observations and face-to-face intercept surveys) and during training sessions. Exercise sessions will run in small groups based on State Government advise. Where possible research meetings and trainings will run online.

### Statistical methods

#### Sample size estimation for intercept surveys

To our knowledge, there are no natural experimental studies that have investigated the usage of exercise equipment following an installation and site activation of specialized outdoor exercise equipment for older people. Studies investigating park visitors before and after park refurbishment (including upgrade of play spaces for children) reported an increase of 33% in park visitors (all ages combined, with 17.3% age between 21–59, and 1.8% age 60 +), with an increase of 112% engagement in moderate physical activity by children and adults [26]. An observational study conducted in NSW reported only 3.8% (*n* = 112) of all visitors utilized outdoor exercise equipment for the purpose of exercise, among these approximately 5.3% (*n* = 6) were older people [18]. Another study reported only 15.6% of park users were older people (60–70 years), with people aged 60–70 being 60% less likely to report being regular park users than the younger age groups [27].

A previous study reported approximately 3 people/visitors every 1.5 h attending a community park [16]. With 3 periods of observations/ scans and total of 5.5 observation hours (early morning, mid-day, late afternoon) per day (estimated 12 people/visitors per day), we then estimate 84 visitors for the 7-day period. Based on a previous study, approximately 15.6–17.9% are expected to be older people [26, 27], hence a sample of 15 older people (17% of 84 visitors) will be expected to be recruited per site at the baseline observation period. With an estimated twofold increase in park visitors following site activation, a sample of 30 face to face intercept interviews will be targeted at the 12 month follow up observation period at each site. With potential 18–20% declining to participate (refusal), we will aim for a total of 38 intercept interviews (13 and 25 at baseline and follow up respectively, which accounts for potential refusals) per site with an overall sample of 228 interviewees across the six sites.

To determine the required sample size, it was assumed that the number of older people visiting the park per week would follow either a Poisson distribution, where the variance equals the mean (no overdispersion), or a negative binomial distribution, where the variance exceeds the mean (overdispersion) [28]. A baseline mean of approximately 15 per week was assumed, corresponding to a coefficient of variation (CV = standard deviation as percentage of mean) for the Poisson distribution of 25.8%. For the negative binomial, the CV was set at 38.7% (a 50% increase in relative variability). In addition, seasonal adjustments to the expected means were made, since it was likely the number of older people visiting the park will be impacted by weather [29]. Fake data simulation was used to determine the power [30]; 10,000 simulated data sets were generated using the Poisson and Negative Binomial distributions assuming a two-fold increase in the number of older people visiting the park. For each data set, the model detailed in the statistical analysis section below was fitted to the data, and the intervention effect was statistically significant at the 5% level for all of the data sets with the Poisson distribution and for over 80% of the data sets with the negative binomial distribution.

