### Assessments

#### Outcome measures

##### Park observation and Seniors Exercise Park equipment usage

Observation of park and exercise equipment visitation and usage will take place prior to site construction (baseline) and at two time points: one month after the site is open for public and 12 months after baseline (Fig. 2). The inclusion of two measures post-refurbishment/construction allows time for residents to become aware of the new facilities [16]. The 12 months evaluation will take place at the same time of the year as the baseline assessments to account for potential seasonal effects.

Evaluation of usage and visitations will include periodic observation (using the System for Observing Play and Recreation in Communities (SOPARC)). The SOPARC is a reliable and feasible instrument for assessing physical activity and associated contextual data in community settings [17]. It is based on momentary time sampling techniques in which systematic and periodic scans of individuals and contextual factors within pre-determined target areas in parks are made. SOPARC was designed to obtain direct information on community park use, including relevant concurrent characteristics of parks and their users. It provides an assessment of park users’ physical activity levels, gender, activity modes/types, and estimated age and ethnicity groupings. Additionally, it provides information on individual park activity areas, such as their levels of accessibility, usability, supervision, and organization. As this study focuses on the usage of the Seniors Exercise Park, we will also collect additional data (not included in the original SOPARC protocol) by coding the interaction with the outdoor exercise equipment (i.e., ‘using equipment as intended’ or ‘playing/looking/sitting’ on the equipment) [18]. We will also note the number of people moving past the equipment area without interacting with the equipment. Each site will be divided into targeted areas to be scanned. Systematic scans will be conducted over a 7-day period (Monday-Sunday) with a total of 11 scans per day as follows (22 and 55 scans for weekend and weekdays respectively): every 30 min of all park visitors in the study area during early morning (07:00–08:30), mid-day (11:30–13:00) and late afternoon (16:00–18:30) [19].

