##### Intercept survey with visitors

Face-to-face intercept surveys (10–15 min) will be conducted at baseline (prior to site construction) and at 12 months follow up during the periodic observation (SOPARC). Trained, clearly identifiable research assistants will approach park users in the specified target areas, and will explain the study and all ethical considerations, and invite participation. Potential participants will be approached and provided with a verbal explanation about the study. Interested participants will then be asked to provide verbal agreement (consent) to participate. If there is more than one person in the park, the research staff will aim to recruit an equal number of men and women. The participants will be eligible to complete only one intercept survey during each test period.

Intercept surveys will provide more in depth information about park users’ characteristics. The survey will include a set of questions across various domains similar to previous research [19, 20] as well as validated questionnaires (detailed below). The set of questions will include socio-economic and demographic characteristics of park users (e.g., age group, gender, if born in Australia, marital status), if they are local residents or visitors, motivation to use the exercise park, how often they visit the park, social connectedness/engagement with other people at the park, their general physical activity level and their leisure/recreation activity at the park, and general health and well being. The following validated questionnaires will be used as part of the survey:

*Self-reported physical activity*—will be measured using three questions from the Active Australia Survey (Australian Institute Of Health And Welfare, 2003 [21]), which assessed walking, moderate, and vigorous activity, plus an indicator of total activity. The Active Australia questions are valid and reliable and are recommended for use in Australian population-based research and will provide measures of time and frequency in light, moderate and vigorous physical activities [22]. The Active Australia questions can also provide a measure as an estimate of energy expenditure in MET-minutes per week.

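### The intercept-survey target of 38 interviews per site (228 overall) does not follow from its stated inputs, because an expected yield is rounded up at each step; unrounded, the inputs give about 190.

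*Protocol article*

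**What the plan says.** All steps are in the Protocol article, under Sample size estimation for intercept surveys, unless noted.

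- Visitor rate: "A previous study reported approximately 3 people/visitors every 1.5 h attending a community park".
- Hours, visitors per day and visitors per week: "total of 5.5 observation hours (early morning, mid-day, late afternoon) per day (estimated 12 people/visitors per day), we then estimate 84 visitors".
- Share of older people: "approximately 15.6–17.9% are expected to be older people". The text then uses 17% of 84 and writes the result as 15 per site at baseline.
- Follow-up: a doubling, giving 30 per site at 12 months.
- Refusal of 18–20%, after which "we will aim for a total of 38 intercept interviews (13 and 25 at baseline and follow up respectively, which accounts for potential refusals"), and 228 over six sites.
- The same baseline figure enters the power simulation: "A baseline mean of approximately 15 per week was assumed".

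Two other sections bear on the point. The section on park observation gives the daily windows as "early morning (07:00–08:30), mid-day (11:30–13:00) and late afternoon (16:00–18:30") and the duration as "Systematic scans will be conducted over a 7-day period (Monday-Sunday"). The section on the intercept survey says: "The participants will be eligible to complete only one intercept survey during each test period".

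**The concern.** The chain predicts how many interviews the field team can expect; it does not derive how many are needed. For a required sample size, rounding up is the cautious direction. For an expected yield it is the optimistic direction. Here the rounding is upward at every step, the baseline excess is doubled at follow-up, and the sum is multiplied by six sites.

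What is at stake is the recruitment expectation. A result near 190 would look like a shortfall against 228, although it is what the stated rates predict. The rounded-up 15 is also the assumed baseline mean of the power simulation.

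**Working it through.** **Inputs (all from the Protocol article).** Rate 3 per 1.5 h = 2 per hour. Observation time 1.5 + 1.5 + 2.5 = 5.5 h per day, which agrees with the stated hours. Seven days. Older share 15.6–17.9%, with 17% used. Doubling at follow-up. Refusal 18–20%. Six sites.

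**Reproducing the plan's figure.** Round up at every step:

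- 5.5 / 1.5 = 3.67 periods, rounded up to 4; 4 × 3 = 12 per day; 12 × 7 = 84 per week.
- 0.17 × 84 = 14.28, rounded up to 15; doubled, 30.
- At 18% refusal: 15 × 0.82 = 12.3, up to 13; 30 × 0.82 = 24.6, up to 25. At 19%: 12.15 and 24.3, again up to 13 and 25.
- 13 + 25 = 38; 38 × 6 = 228.

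So 228 comes out exactly when each step is rounded up and refusal is 18% or 19%. At 20% refusal even this chain gives 12 + 24 = 36 per site and 216 overall.

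**The steps without rounding.**

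| Step | Stated | From the stated inputs |
|---|---|---|
| Visitors per day | 12 | 2 × 5.5 = 11 |
| Visitors per week | 84 | 11 × 7 = 77 |
| Older people, baseline | 15 | 0.17 × 84 = 14.28; 0.17 × 77 = 13.09 |
| Older people, 12 months | 30 | 2 × 13.09 = 26.18 |
| Interviews from 15, baseline | 13 | 15 × (0.80 to 0.82) = 12.0–12.3 |
| Interviews from 30, 12 months | 25 | 30 × (0.80 to 0.82) = 24.0–24.6 |

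The stated 13 of 15 and 25 of 30 imply refusal of 1 − 13/15 = 13.3% and 1 − 25/30 = 16.7%. Both lie below the stated 18–20%.

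**Overall total** = 6 × (baseline + follow-up) × (1 − refusal).

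- 11 per day, 17% older: 6 × 39.27 × (0.80 to 0.82) = 188.5–193.2, or 31.4–32.2 per site; at 19% refusal, 190.9. By wave: 13.09 × (0.80 to 0.82) = 10.5–10.7 and 26.18 × (0.80 to 0.82) = 20.9–21.5.
- 11 per day, full stated ranges: 6 × 36.04 × 0.80 = 173.0 to 6 × 41.35 × 0.82 = 203.4.
- 12 per day accepted, 17% older: 6 × 42.84 × (0.80 to 0.82) = 205.6–210.8.
- 15 and 30 accepted: 6 × 45 × (0.80 to 0.82) = 216.0–221.4.
- Most favourable unrounded case, 12 per day, 17.9% older and 18% refusal: 0.179 × 84 = 15.04; 6 × 45.11 × 0.82 = 221.9.

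None of these reaches 228. Against 188.5–193.2 it is 18–21% high (228/193.2 = 1.18; 228/188.5 = 1.21). Against 216.0–221.4 it is 3–6% high (228/221.4 = 1.03; 228/216 = 1.06).

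**Persons and visits.** The chain adds visitors over time slots and days and treats each as a possible interview. Someone who comes on several days is counted each time but may be interviewed once per period. The figures above are therefore upper bounds if there are repeat visits. The article gives no repeat-visit rate, so no size can be attached to this.

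**The case against.** The strongest reply is that this is an openly approximate feasibility estimate. The source rate is itself approximate, so 11 against 12 per day is a soft difference. The quoted share runs up to 17.9%, and 17.9% of 84 is 15.04, so 15 lies within the plan's own range and only the bracketed 17% is loose. From 15 and 30 the excess is 7–12 interviews of 228. This stands as a limit on the size of the error. It does not remove the error: 17% of 84 is still not 15, and the refusal step fails even when everything before it is accepted.

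It also stands that 228 is an aim and not a power-based requirement. The Statistical analysis section plans descriptive statistics for the survey, so no test depends on this number.

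Three stronger readings are tempting, and the documents do not support them.

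- **That power falls below the stated level.** With a mean of 13.1 the Poisson CV is 1/√13.09 = 27.6% instead of 25.8%, so some loss is plausible. The seasonal adjustments are not given, however, so the simulation cannot be reproduced. With an assumed seasonal layout and a single intervention term, as the analysis section specifies, simulated power was about 0.86 at mean 15 and 0.84 at 13.1. A model with a separate 12-month contrast, which is not the specified model, gave 0.797 at mean 13 in one run. That is within Monte Carlo error of 0.80 (about 0.4 points with 10,000 data sets).
- **That repeat visits roughly halve the yield, to about 95.** This assumes two visits per older person in the week, a figure found nowhere in the article.
- **That the target will drive over-recruitment by convenience.** No mandatory quota is set, and interviews are confined to the same seven days as the scans.

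**Conclusion.** The stated target contradicts its own inputs at three places: the daily count, the older share, and the refusal step. Every discrepancy goes in the favourable direction. The best single figure from the stated rates is about 190 interviews. It rests on 11 visitors per day, 17% older people and mid-range refusal; the full stated ranges give 173–203. A reader who accepts 12 per day gets 206–211, and one who accepts 15 and 30 gets 216–221. The unrounded arithmetic does not give 228 under any of these readings.

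The consequence is limited. A recruitment expectation and its stated derivation need correcting; no planned test or error rate is made invalid. The baseline mean of 15 in the power simulation has the same origin, which makes a check at about 13 reasonable, but loss of the claimed power is not shown.

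**What to change.** Restate the chain without upward rounding: 11 visitors per day, 77 per week, about 13 older people at baseline and 26 at 12 months, about 10–11 and 21 interviews per site, and about 190 overall with the range 173–203. If the sponsor prefers to keep 12 per day or the 17.9% share, it should say so and carry those values through consistently, including the refusal step. Describe the result as an expected number of interviews, and add that it is an upper bound if people visit more than once in the week, because each person is surveyed once per period.

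As an optional check, rerun the existing power simulation with a baseline mean of about 13 and report the result beside the one at 15.

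The cost is a few sentences of text and, if the check is done, one rerun of existing code. Design, data collection and analysis do not change; the stated number of interviews becomes less favourable.

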#### A targeted outcome for ENJOY MAP for HEALTH project

A study investigating the impact of major renovations to playfields (mainly used for soccer and baseball) of two public parks as well as physical activity programming, reported a significant increase in visitation and overall physical activity (4-9 fold increase) compared to the controls [31]. This suggests that intervention that includes change in the physical built environment complemented with other community engagement is likely to result in substantial increase in physical activity participation. With limited studies reporting older people’s usage and engagement in physical activity, we estimate a twofold increase in visits by older people from baseline to the 12 months follow up at each site. Hence, we hypothesise that the intervention (Seniors Exercise Park installation and site activation) will result in *at least* twofold increase (100%) in the number of visitors (older people) between baseline to the 12 months follow up.

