#### Statistical analysis

Descriptive statistics will be used to report the overall park observation visitors, visitors’ characteristics, prevalence of usage of the Seniors Exercise Park, the type and level of physical activity of visitors (SOPARC). Descriptive statistics will also be used for the intercept surveys data to collate information about visitors’ perceptions about the park, motivation to use it, social connectedness/engagement with other at the park, their physical activity level and general wellbeing and their leisure/recreation activity at the park.

A generalised linear model [28] will be used to examine the effects of park refurbishment (equipment installation and site activation) on the total number of older people observed in the park, and the number of people walking and being physically active in the park. The statistical model will include terms for the intervention effect, the site effects, and seasonal effects; and overdispersion will be handled by using a quasipoisson family [32]. Statistical analyses will conducted using IMB SPSS Statistics version 26 (IBM Corporation, Armonk, NY, USA) and R [33].

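### The stated power is for detecting any change when visits truly double, so it does not apply to the hypothesis of an at least twofold increase

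*Protocol article*

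**What the plan says.** In the protocol article, *A targeted outcome for ENJOY MAP for HEALTH project* first gives an expected value: "we estimate a twofold increase in visits by older people from baseline to the 12 months follow up at each site". The next sentence turns that value into a floor. It hypothesises, with the words *at least* emphasised, a "twofold increase (100%) in the number of visitors (older people) between baseline to the 12 months follow up". This is the only formal hypothesis in the article.

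The power statement is in *Sample size estimation for intercept surveys*. Data were simulated "assuming a two-fold increase in the number of older people visiting the park". Without overdispersion, the reported result is that "the intervention effect was statistically significant at the 5% level for all of the data sets with the Poisson distribution". With overdispersion, the same criterion was reported as met "for over 80% of the data sets with the negative binomial distribution".

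The planned model is under *Statistical analysis*: "The statistical model will include terms for the intervention effect, the site effects, and seasonal effects", with a quasi-Poisson variance. No section names 2 as a null value or says how the estimate will be judged against a doubling.

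**The concern.** A hypothesis that the ratio is at least 2 and a test that the ratio differs from 1 are different claims. The first is supported when the data exclude ratios below 2, the second when they exclude 1. The article gives power for the second beside a hypothesis of the first kind.

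What is at stake is the conclusion the trial may draw. A significant intervention term would be compatible with a true increase well short of doubling. A true doubling, exactly as planned, would almost never be enough to show that the increase is at least twofold. A reader who takes the quoted power as the chance of confirming the stated hypothesis would be badly misled.

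**Working it through.** **Inputs from the article.**
- Six sites (*Study setting and partners*).
- Three observation waves per site: baseline, one month after opening, and 12 months after baseline (*Park observation and Seniors Exercise Park equipment usage*).
- "A baseline mean of approximately 15 per week was assumed".
- "For the negative binomial, the CV was set at 38.7% (a 50% increase in relative variability").
- A true ratio of 2, the 5% level, and a quasi-Poisson model with intervention, site and season terms.

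**Negative binomial parameter.** The Poisson CV is 1/√15 = 25.8%, and 1.5 × 25.8% = 38.7%, as stated. The variance is (0.3873 × 15)² = 33.75. Solving 15 + 15²/k = 33.75 gives k = 225/18.75 = 12.

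**Assumptions not in the article.** Log link, two-sided test, equal site means, one ratio common to both follow-up waves, k constant across waves and, where season terms are fitted, seasonal multipliers of 0.8–1.2.

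**Step 1: reproduce the stated power** (10,000 data sets per scenario, null ratio 1, true ratio 2).

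| Model | Poisson | Negative binomial |
|---|---|---|
| Three waves, season terms | 99.98% | 87.1% |
| Three waves, no season terms | 100% | 91.8% |
| Baseline and 12 months only | 99.0% | 75.3% |

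The three-wave models fit the article's figures. The two-wave model falls short of them for the negative binomial and is not used further.

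**Step 2: same fits, judged against ratio 2.** Each cell gives three waves with season terms / three waves without.

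| True ratio | Lower 95% limit above 2, Poisson | Lower 95% limit above 2, negative binomial |
|---|---|---|
| 2 | 2.2% / 2.2% | 1.8% / 1.5% |
| 2.5 | 39% / 42% | 12% / 12% |
| 3 | 89% / 92% | 35% / 37% |
| 4 | about 100% / about 100% | 82% / 85% |

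**Step 3: a true ratio below the hypothesis.** At a true ratio of 1.5 the effect differs significantly from 1 in 82% / 87% of Poisson data sets and 42% / 47% of negative binomial ones.

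**Hand check (Poisson, three waves, no season terms).** There are 6 baseline and 12 follow-up counts. The model has 7 parameters, leaving 18 − 7 = 11 residual df and a t quantile of 2.201. For a true ratio R, the variance of the log ratio is 1/(6 × 15) + 1/(12 × 15R).
- R = 2: 1/90 + 1/360 = 0.01389, SE 0.118, half-width 2.201 × 0.118 = 0.259. An estimate of 2.0 has a 95% interval of 2·exp(±0.259) = 1.54 to 2.59, so an estimate of about 2.6 is needed before the lower limit passes 2.
- R = 3: 1/90 + 1/540 = 0.01296, SE 0.114, half-width 0.251. (ln 1.5 − 0.251)/0.114 = 1.36, or about 91% against ratio 2 (simulated 92%).
- R = 1.5: 1/90 + 1/270 = 0.01481, SE 0.122, half-width 0.268. (ln 1.5 − 0.268)/0.122 = 1.13, or about 87% against ratio 1 (simulated 87%).

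**The case against.** The power statement does not misreport itself. It gives both its assumed effect and its success criterion, and never claims power to exclude ratios below 2. The targeted-outcome section moves from an estimate to a hypothesis, so it can be read as an expected effect loosely worded. The roughly 2% at a true ratio of 2 follows for any test evaluated at its own boundary and shows no special weakness of this design. How an estimate will be set against a target is often left to a fuller plan.

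Much of this stands. A reader might go further and infer that the design cannot confirm its own hypothesis. The article does not support that: the planned model yields a ratio whose interval can be compared with 2, power against 2 is substantial at a true ratio of 3 to 4, and the article itself cites an earlier study with a 4- to 9-fold increase. A reader might also infer that the investigators will treat significance as proof of a doubling. No section says so; the analysis section only sets out to examine the effects. Nor does any section make success depend on the point estimate reaching 2.

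What the objection does not remove is that hypothesis and power are both stated in the article and do not match. A later analysis plan could add a rule for comparing the estimate with 2, but it could not make the published power apply to that rule.

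**Conclusion.** The point holds as a mismatch between the stated hypothesis and the stated power. The quoted power is for a ratio different from 1 at a true ratio of 2. For the claim of at least twofold, the chance of success at that same planning value is about 1–2%, and it becomes good only when the true ratio is well above 2: about 3 if counts are Poisson, about 4 if they are overdispersed as the article allows.

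The null of no change is not written out in the article. It is inferred because the stated power can be reproduced against ratio 1 and not against ratio 2. The exact percentages depend on the assumptions listed in the working; the range shown covers models with and without season terms, and the conclusion is the same in both.

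**What to change.** Change the wording in two places and add one reporting rule.

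1. In the targeted-outcome section, state the tested hypothesis as an increase in older visitors from baseline to 12 months (ratio above 1), with twofold as the planning value.
2. In the sample size section, say that the quoted power is for a ratio different from 1 when the true ratio is 2.
3. In the analysis section, report the ratio with its 95% confidence interval, and conclude at least twofold only if the lower limit is at or above 2.

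If the investigators wish to keep at least twofold as the tested hypothesis, they should name 2 as the null value and give power for a true ratio above 2.

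Data collection, model and sample size stay as they are. The cost is a less ambitious headline hypothesis.
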